## Blinding

Whereas patients and physicians allocated to the intervention group be aware of the allocated arm, outcome assessors and data analysts will be kept blinded to the allocation.

## Data management

**Anonymity and data security**

All participant information will be stored without their names or personal identification, or any other information which may reveal their identity. A special code will attach results and samples to a list of names. This list will only be accessible for selected authorised personnel performing this research.

**Access to source data**

According to the ICH-GCP and the applicable Chinese laws, the coordinating investigator must allow access to all authorised third parties to the trial site and insight into the source data. This permission includes the medical committee, clinical trial monitors, and authorised members of the Local Government.

**Monitoring**

Three regular visits will be scheduled. The reason for these visits is to check the compliance of the trial with the study protocol. This control includes a check of the informed consent documents of all participants, source data verification of the key data (eligibility criteria, components of the primary outcome, safety aspects) of all participants.

# INDIVIDUAL TRIAL PROCEDURE AND OUTCOMES ASSESSMENT

Table 2. Summary of the examinations

|  | T1 | T2 | T3 | | | T4 | T5 | | |
| --- | --- | --- | --- | --- | --- | --- | --- | --- | --- |
|  |  |  | T3A | T3B | T3C |  | T5A | T5B | T5C |
| Randomization | X |  |  |  |  |  |  |  |  |
| Demographics | X |  |  |  |  |  |  |  |  |
| Anthropometric assessment | X |  |  |  |  |  |  |  |  |
| Physical activity habit | X |  |  |  |  |  |  |  |  |
| Diet - food frequency questionnaire | X |  |  |  |  |  |  |  |  |
| Medical history | X |  |  |  |  |  |  |  |  |
| Medication history | X |  |  |  |  |  |  |  |  |
| ECG | X |  |  |  |  |  |  |  |  |
| Perceived Stress Scale | X |  |  |  |  |  |  |  |  |
| Generalized Anxiety Disorder Scale | X |  |  |  |  |  |  |  |  |
| Patient Health Questionnaire | X |  |  |  |  |  |  |  |  |
| Cardiopulmonary exercise testing | X |  |  |  |  |  |  |  |  |
| Whole blood collection, non-specific proteomics |  |  | X |  | X |  | X |  | X |
| Gas exchange parameters during exercise |  |  |  | X |  |  |  | X |  |
| Heart rate and blood pressures during exercise |  |  |  | X |  |  |  | X |  |

T1 = At enrollment (week 0); T2 = 2 weeks washout period after cardiopulmonary exercise testing (2^nd^ week); T3 = First exercise intervention (4^th^ week); T3A = 5 minutes before training; T3B = During HIIT/MICT training; T3C = 15 minutes after training; T4 = 2 weeks washout period for alternating between the two types of exercise; T5 = Second exercise intervention (6^th^ week); T5A = 5 minutes before training; T5B = During HIIT/MICT training; T5C = 15 minutes after training.

**Clinical assessment and exercise preparticipation screening**

The screening will take place following the initial enrolment and will take place in two visits. All participants will be screened by medical history and assessed with a physical examination and physical activity assessment in the initial visit. After the initial assessments, those who meet the inclusion criteria and meet the criteria for sedentary lifestyle will be screened in the second round of examinations. Examinations will be performed according to standard operating procedures and will include anthropometry, electrocardiogram, and cardiopulmonary exercise testing. The investigators conducting the evaluations will not be performing the randomisation at baseline testing.

**Demographics and physical activity assessment**

- Body weight, height, and BMI
- Physical activity: International Physical Activity Questionnaire-Short Form
- Diet - Food Frequency Questionnaire

**Clinical Data**

- Medical history
- Medication history
- Blood biochemical tests: fasting blood glucose (FBG), insulin sensitivity, complete blood count, glucose and lipid profiling, liver function and kidney function tests
- Resting electrocardiogram
- Stress level - Perceived Stress Scale
- Generalized Anxiety Disorder Scale (GAD-7)
- Patient Health Questionnaire (PHQ-9)

**Blood collection**

In this study, professional medical personnel will perform 4 venous blood collections for each participant, corresponding to before and after the two exercise interventions. Each blood collection will be 10 ml, collected using non-anticoagulant tubes, left at room temperature for 2 hours, then centrifuged at 2-8℃ at 1000g for 15 minutes, and the supernatant is taken and stored at -20℃ or -80℃ for subsequent testing and analysis.

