Previous research on the mechanisms of exercise has largely centered on understanding how exercise affects specific molecules or pathways, constrained by the available research methodologies. Prior findings have demonstrated that exercise can positively influence mitochondrial quality control in both skeletal and cardiac muscles of mice. This is achieved through the activation of AMPK, which leads to improvements in insulin resistance and an enhancement in stress resistance. [8-12]. Recently, the development of multi-omics technologies and bioinformatics has provided methods to explore comprehensive exercise responses. Using these methods, researchers like Contrepois [13] and Whitham [14] have reported the acute molecular responses of healthy adults to a single session of moderate-intensity exercise. In their studies, during a single session of moderate-intensity exercise thousands of molecular changes and biological processes were revealed, including energy metabolism, oxidative stress, inflammatory responses, tissue repair, growth factor responses, and regulatory pathways. The comprehensive proteomic characteristics between different exercise intensities are not yet clear and have not been reported.

This study intends to use a crossover trial design, employing non-specific proteomics techniques and bioinformatics methods to map the molecular responses of adult plasma to MICT and HIIT. This research will be the first to explore proteins specifically and co-expressed in both forms of exercise, providing data support and direction for subsequent research in precise exercise therapy; it will also provide information for the development of exercise mimetics, allowing patients who are unable to participate in exercise due to functional impairments to also gain the health benefits associated with exercise.

**We hypothesize** that the HIIT will induce a distinctive plasma protein response in contrast to MICT.

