## Objectives

**Primary Objective**

To delineate the proteomic responses in adult plasma following MICT and HIIT.

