## Outcomes

**Primary outcome**

Any differentially expressed plasma proteins or metabolic molecules observed after HIIT and MICT.

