**Proteomics procedures**

**Protein extraction**

Frozen samples (about 100 mg) will quickly be ground into fine and uniform powder in liquid nitrogen and then homogenized in 1 mL phenol extraction buffer, after which 1 mL saturated phenol with TrisHCl (pH 7.5) will be added. After several times’ shake, the mixture will be kept at 4℃ for 30 min. The upper phenolic phase will be separated from the aqueous phase by centrifugation at 7100 g at 4℃ for 10 min, transferred to a fresh tube and mixed with five volumes of pre-cold 0.1 M ammonium acetate-methanol. After being kept at −20℃ overnight, the mixture will be centrifuged at 12,000 g for 10 min at 4℃ to pellet precipitated protein. For wash step, the pellet will be resuspended twice with pre-cold methanol and twice with ice-cold acetone. Following another round of centrifugation, the pellet will be collected, air-dried and resuspended with 300 μL lysate solution. After incubation of 3 hr at room temperature, the solution will be centrifuged to remove any insoluble fraction and the resulting supernatant will contain the total extractable protein. The total protein concentrations will be quantified by bicinchoninic acid assay.

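### The blood-handling procedure produces serum, but the aim, hypothesis, objective and outcomes are all stated for plasma

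*Protocol*

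**What the plan says.** The Blood collection text in section 5 sets a single rule for "4 venous blood collections for each participant, corresponding to before and after the two exercise interventions". It reads "Each blood collection will be 10 ml, collected using non-anticoagulant tubes, left at room temperature for 2 hours". The tubes are then centrifuged, after which "the supernatant is taken and stored at -20℃ or -80℃ for subsequent testing and analysis".

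The scientific statements name a different matrix:

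- The primary objective (section 3.2) reads "To delineate the proteomic responses in adult plasma following MICT and HIIT".
- The hypothesis (section 3.1) is "that the HIIT will induce a distinctive plasma protein response in contrast to MICT".
- The primary outcome (section 4.6) is "Any differentially expressed plasma proteins or metabolic molecules observed after HIIT and MICT".
- The aim and the primary outcome in the Synopsis, and the secondary outcome in section 4.6, also say plasma, as does the opening of the sample-size paragraph (section 4.4).

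**The concern.** Serum and plasma are different specimens. Plasma is the liquid part of blood that has been kept from clotting. Serum is what is left after a clot has formed and been removed: it has lost the proteins used up in the clot and gained material released by platelets and other cells while the clot formed. A tube without anticoagulant, left standing for two hours and then centrifuged, gives serum.

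The protocol therefore defines its primary outcome in one matrix and fixes collection in another. The objective is an untargeted description of the plasma response, so the proteins that clotting affects fall inside the endpoint. If the results are reported under the protocol's own label, readers will take them as statements about plasma proteins that the procedure did not measure in plasma.

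**Working it through.** No sample-size or power figure is in dispute, so the check is mainly a comparison of texts.

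**Step 1. How many samples the rule covers.** Section 4.4 needs 8 participants and allows for 20% dropout: 8 / (1 - 0.20) = 10. Blood collection sets 4 draws each: 10 x 4 = 40 planned samples. All 40 come under the same tube, standing time and centrifugation. The inputs to the 8 (difference 21.9, SD 15.0, alpha 0.05, power 0.8) were taken from fasting glucose and do not involve the specimen type, so neither 8 nor 10 changes with the matrix.

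**Step 2. What the rule yields.** No anticoagulant, two hours at room temperature, centrifugation, supernatant kept: serum.

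**Step 3. Whether another part of the protocol resolves it.**

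| Place | What it says about the specimen |
| --- | --- |
| Synopsis, aim and primary outcome | plasma |
| 3.1 Rationale, hypothesis | plasma |
| 3.2 Primary objective | plasma |
| 4.6 Primary and secondary outcomes | plasma |
| Table 1 (visit schedule) | venous blood, no tube named |
| Table 2 (examinations) | whole blood, no tube named |
| 5 Blood collection | no anticoagulant, clotting time, supernatant |
| 5 Protein extraction | frozen samples, matrix not named |

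No entry describes an anticoagulated tube or a separate plasma aliquot, and the protocol never calls the study sample serum. The conflict stands.

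**Step 4. What it does to the contrasts.** For one protein, let P be its plasma level and k the proportion of signal that survives or is gained through clotting, so the serum level is S = kP.

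- If k is the same at every draw, the pre/post ratio is kP_post / kP_pre = P_post / P_pre. The constant cancels, and it also cancels when the HIIT ratio is divided by the MICT ratio.
- If clotting instead adds a fixed amount r, differences are unchanged. The ratio (P_post + r) / (P_pre + r) lies between 1 and P_post / P_pre, so a fold change may shrink but none is created.
- If k is close to zero because the protein is consumed in the clot, there is little or nothing to measure, and its plasma response cannot be described from these tubes.
- If exercise changes k, the pre/post ratio is multiplied by k_post / k_pre. The HIIT/MICT comparison is distorted only if that factor differs between the two sessions.

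The documents give no value for k or r and do not discuss clotting or platelet release. Table 2 lists no platelet count at the exercise draws; the complete blood count under Clinical Data is not tied to them. The last case can be neither sized nor ruled out from the protocol.

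**The case against.** The strongest reply is that this is a matter of labelling. All four draws are treated alike, each participant is his own control, and a constant clotting effect drops out of the comparisons that matter. That is correct as far as it goes. It protects the contrasts against a constant effect, but it does not turn serum into plasma or recover proteins lost to the clot.

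Three stronger readings may tempt a reader, and the documents do not support them:

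- *That clotting produces spurious exercise effects here.* This needs exercise, or its intensity, to change what clotting consumes or releases. Nothing in the protocol says so. It remains an unquantified possibility.
- *That the trial can say nothing about plasma proteins.* This is too absolute. The problem concerns proteins that clotting removes or releases, and their number and the size of the effect cannot be derived from the protocol.
- *That the storage and extraction texts add further contradictions.* Allowing two storage temperatures does not say that one participant's samples will be split between them. A supernatant that has been frozen can be weighed and ground as the extraction text describes.

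It may also be said that collection is over: the Statistical methods section ends in the past tense and the CONSORT checklist gives page references for results. The documents do not state the collection status outright. If blood has been drawn, that decides which remedy applies; it does not remove the contradiction.

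**Conclusion.** The contradiction is real and nothing else in the protocol resolves it. The specified procedure yields serum in all 40 planned samples, while the aim, hypothesis, primary objective, primary outcome and secondary outcome are stated for plasma. For proteins consumed in or released during clotting, conclusions about the plasma proteome are not supported.

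Bias in the pre/post or HIIT/MICT contrasts is not established. It would arise only if exercise altered the clotting contribution, and its size cannot be derived here.

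The conclusion rests on the Blood collection text being followed as written and on the ordinary definitions of serum and plasma. It does not depend on any figure in the sample-size section.

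**What to change.** Make specimen and outcome agree by one of two routes.

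- **If samples have not been drawn:** amend Blood collection to an anticoagulant tube with prompt centrifugation, and keep the plasma wording.
- **If samples have been drawn as described:** replace *plasma* with *serum* in the aim, hypothesis, objective and outcomes, and in the sample-size paragraph, which uses the same term. State that changes in clotting- and platelet-derived proteins are to be interpreted with caution.

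As an optional minor tightening, use one storage temperature for all four samples of a participant.

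The cost is a different tube or a wording amendment. Sample size, visit schedule and number of draws stay as they are.

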**Proteomics procedures**

**Protein extraction**

Frozen samples (about 100 mg) will quickly be ground into fine and uniform powder in liquid nitrogen and then homogenized in 1 mL phenol extraction buffer, after which 1 mL saturated phenol with TrisHCl (pH 7.5) will be added. After several times’ shake, the mixture will be kept at 4℃ for 30 min. The upper phenolic phase will be separated from the aqueous phase by centrifugation at 7100 g at 4℃ for 10 min, transferred to a fresh tube and mixed with five volumes of pre-cold 0.1 M ammonium acetate-methanol. After being kept at −20℃ overnight, the mixture will be centrifuged at 12,000 g for 10 min at 4℃ to pellet precipitated protein. For wash step, the pellet will be resuspended twice with pre-cold methanol and twice with ice-cold acetone. Following another round of centrifugation, the pellet will be collected, air-dried and resuspended with 300 μL lysate solution. After incubation of 3 hr at room temperature, the solution will be centrifuged to remove any insoluble fraction and the resulting supernatant will contain the total extractable protein. The total protein concentrations will be quantified by bicinchoninic acid assay.

**Protein digestion**

According to the measured protein concentration, the same quality protein from each sample will be taken, and different groups of samples will be diluted to the same concentration and volume. Furthermore, 25 mM DTT of corresponding volume will be added into the above protein solution to make the DTT final concentration about 5 mM, and incubate at 55℃ for 30-60 min. Then the corresponding volume of iodoacetamide will be added so that the final concentration is about 10 mM, and place in the dark for 15-30 min at room temperature. Then 6 times the volume of precooled acetone in the above system to precipitate the protein, and place it at - 20°C for more than four hours or overnight. After precipitation, the sample will be taken out and centrifuged at 8000 g for 10 min at 4℃ for collecting the precipitate. According to the amount of protein, the corresponding volume of enzymolysis diluent (protein: enzyme = 50:1 (m/m), 100 μg of protein add 2 μg of enzyme) will be added to redissolve the protein precipitate, then the solutions will be incubated for digestion at 37 ℃ for 12 h. The samples will be desalted on SOLA™ SPE. After drying under vacuum, samples will be resuspended and iRT peptides (1:10) will be added.

**High-pH reversed-phase fractionation**

The peptide of pooled samples will be fractionated by 1100 HPLC System (Agilent). Mobile phases A (2% acetonitrile in HPLC water) and B (98% acetonitrile in HPLC water) will be used for RP gradient. The solvent gradient will be set as follows: 0~10 min, 98% A; 10~10.01 min, 98%95% A; 10.01~37 min, 95%80% A; 37~48 min, 8060% A; 48~48.01 min, 6010% A; 48.01~58 min, 10% A; 58~58.01 min, 1098% A; 58.01~63 min, 98% A. Tryptic peptides will be separated at a fluent flow rate of 250μL/min and monitored at 210 nm. Samples will be collected for 10-50 min, and eluent will be collected in centrifugal tube 1-10 every minute in turn. Samples will be recycled in this order until the end of gradient. The separated peptides will be lyophilized for mass spectrometry.

**Data dependent acquisition (DDA) and data independent acquisition (DIA) Mass spectrometry analysis**

The Proteomic data analysis will be performed by Shanghai Luming biological technology co., LTD (Shanghai, China). TimsTOF Pro mass spectrometer (Bruker) and Easy nanoLC-1200 (Thermo Fisher Scientific) will be used for both shotgun proteomics and DIA experiments. Samples will be loaded and separated by a C18 column (50 cm × 75 µm) on an EASY-nLCTM 1200 system (Thermo, USA). The flow rate will be 300 nL/min and linear gradient will be 90 min (0~45min, 5%B; 45~50 min, 27% B; 50~55 min, 100% B; 55~60 min, 100% B; mobile phase A = 0.1% FA in water and B = 0.1% FA in 80%ACN).

For data dependent acquisition (DDA), full scan MS spectra will be acquired at the resolution of 35,000, with the automatic gain control (AGC) target set as 1e6. The top 10 intense ions will be isolated for HCD MS/MS fragmentation. For data independent acquisition (DIA), a survey scan from 350 to 1250 m/z at 35,000 resolution will be adopted. Then, 26 DIA windows will be acquired and the stepped collision energy will be 28eV.

**Database search**

The default factory settings will be used for the Spectronaut Pulsar™ (Biognosys, Swiss) search and library generation (including Trypsyin/P as enzyme, up to two missed cleavages allowed, Oxidation of Me as variable modifications, carbamidomethyl of C as fixed modification, and 1% FDR for PSM, peptide and protein identification). The DDA search results will be imported into Spectronaut Pulsar™. The DIA data will be analysed with Spectronaut searching the above constructed spectral library. The main parameters of the software will be set as follows: retention time prediction type will be dynamic iRT, interference on MS2 level correction will be enabled, and cross run normalization will be enabled. All results will be filtered based on Q value cutoff 0.01 (equivalent to FDR < 1%).

**Cardiopulmonary exercise testing**

All participants will be tasked to perform a cardiopulmonary exercise testing with individually tailored ramp protocols on cycle ergometry on V2. The workload for the cardiopulmonary exercise testing will gradually be increased each minute by a workload calculated as the value of the predicted maximal work rate divided by 8 to 12 according to the individual’s health condition and activity habit so that the duration of cardiopulmonary exercise testing fits within 8-12 min.

A 12-lead ECG will be monitored continuously, and blood pressure will be measured by manual sphygmomanometry at rest and during the last 20-30 seconds of every two minutes. Oxygen saturation will also be monitored continuously via finger oximetry. Participants will be asked to score the Rating of Perceived Exertion accordingly (RPE, Borg 6-20) at the end of each stage.

Participants will be encouraged to continue exercising until they present with at least one of the following termination criteria:

1. achievement of ≥ 85% predicted maximal heart rate (predicted maximal heart rate = 220 - age);
2. plateau in heart rate with increasing workload;
3. plateau in oxygen consumption with increasing workload;
4. respiratory exchange ratio (RER) of ≥ 1.10;
5. rating of perceived exertion (RPE) ≥ 17 (Borg 6 - 20 scale);
6. angina increasing to 3 on a scale of 4;
7. severe fatigue or dyspnea;
8. a decrease in systolic blood pressure with increasing work rate;
9. severe supraventricular or ventricular arrhythmias;
10. signs of poor peripheral perfusion; or
11. the participant’s request to stop.

After test completion, a cool-down will be performed, with continued ECG monitoring, for 6 minutes or longer if the participant is symptomatic or if blood pressure, heart rate, and ST segments have not returned to near baseline values.

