**Intervention protocols:**

**(1) MICT:** The MICT protocol consists of a 1-minute warm-up, followed by training at 50% maximum exercise capacity for 36 minutes, and concluding with a 4-minute cooldown, resulting in a total exercise duration of 41 minutes.

**(2) HIIT:** HIIT involves a 5-minute warm-up, followed by four repetitions of high-intensity training and a low-intensity recovery cycle, and ends with a 4-minute cooldown, also totaling 41 minutes. Each cycle of HIIT includes 4 minutes of high-intensity training at 70% maximum exercise capacity, followed by 4 minutes of low-intensity training at 30% maximum exercise capacity.

**Time plan:** Start: May 2023

First inclusion of participants: May 2023

Inclusion of all participants: Dependent

All participants completed the study: Dependent

**Statistical analysis:** The proteomic data will be analysed by an expert who is good at bioinformatics.

**
[figure not shown]
Flow chart**

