## Interventions

**Training intervention**

**Type**: Bicycle.

**Setting**: Xiangya Hospital, Central South University, Changsha, China.

**Protocol:** A brief description of the exercise program is as follows:

- MICT: The MICT protocol consistes of a 1-minute warm-up, followed by training at 50% MEC for 36 minutes, and concluding with a 4-minute cooldown, resulting in a total exercise duration of 41 minutes.
- HIIT: The HIIT involves a 5-minute warm-up, followed by four repetitions of high-intensity training and a low-intensity recovery cycle, and ends with a 4-minute cooldown, also totaling 41 minutes. Each cycle of HIIT includes 4 minutes of high-intensity training at 70% MEC, followed by 4 minutes of low-intensity training at 30% MEC.

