**Tests and associated risks**

If the participants fulfil the inclusion criteria and do not meet any condition that would exclude them from the study, we will perform several tests on each subject: cardiopulmonary exercise with cycle ergometry, assessments of measures of height, weight, waist:hip-ratio, in addition to health-related questionnaires. These tests will be performed before the training period. After testing, participants will be randomised to an exercise group or to a control group receiving modern advice.

Although the risk of an adverse event or serious adverse events is elevated during exercise compared to rest, this absolute increase of risk is low, and it is generally accepted that the benefits brought about by exercise outweigh the low-risk of adverse events. The cardiopulmonary exercise tests are aborted when the participant can no longer sustain or increase the exercise load, or by signs of ischemia and are undertaken with the supervision of clinicians. We recently published an article finding that cardiopulmonary exercise testing is a relatively safe form of testing in Chinese patients. The team has good experience in undertaking cardiopulmonary exercise testing and risk management.

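### Both regimens are dosed as a percentage of maximum exercise capacity, but the only capacity test may be stopped at 85% of predicted maximal heart rate, so the loads can be scaled to a submaximal value

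*Protocol*

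**What the plan says.** Section 4.5 (Interventions) prescribes MICT as "training at 50% MEC for 36 minutes" and HIIT as four cycles: "Each cycle of HIIT includes 4 minutes of high-intensity training at 70% MEC, followed by 4 minutes of low-intensity training at 30% MEC". The Synopsis spells the abbreviation out: "4 minutes of high-intensity training at 70% maximum exercise capacity". Neither place says how MEC is obtained or in what unit.

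The only capacity measurement in the protocol is the cycle cardiopulmonary exercise test, marked once in Table 2 (at T1). Section 5 (Cardiopulmonary exercise testing) has participants encouraged to go on "until they present with at least one of the following termination criteria". Eleven criteria follow. The first is "achievement of ≥ 85% predicted maximal heart rate", with predicted maximum given as 220 minus age. The list also holds plateaus in heart rate and oxygen uptake, RER of at least 1.10, RPE of at least 17, severe fatigue or dyspnoea, the participant's request, and clinical safety stops such as angina, arrhythmia and a falling systolic pressure.

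The ramp in the same section rises each minute by the "predicted maximal work rate divided by 8 to 12", chosen individually "so that the duration of cardiopulmonary exercise testing fits within 8-12 min".

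Section 6.3 (Tests and associated risks) describes the end of the test differently: it is "aborted when the participant can no longer sustain or increase the exercise load", or for signs of ischaemia.

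**The concern.** A load expressed as a percentage of maximum means what it says only if the maximum was approached. Section 5 calls its items termination criteria, and any one is enough. In men aged 30-35 a stop at 85% of age-predicted heart rate can come well short of maximum, and nothing in the protocol asks for maximal effort, a verification bout or extrapolation. Section 6.3 describes an effort-limited test, and the protocol does not say which description governs.

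The trial's hypothesis is that HIIT produces a plasma protein response distinct from that of MICT. If the scaling value is submaximal, both sessions are easier than labelled and closer together in absolute intensity, so a weak difference could reflect the dose delivered. If some of the 10 participants stop at 85% and others at exhaustion, the same named percentage is a different relative load in different men.

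**Working it through.** **Inputs from the protocol.** Age 30-35 (section 4.3). Predicted maximal heart rate 220 - age, stop at 85% of it, ramp divisor 8 to 12 and target duration 8-12 min (section 5). Loads 70/50/30% MEC (section 4.5).

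**Inputs assumed, not in the protocol.** MEC is the peak work rate reached on the test. Heart rate is linear in work rate. Resting rate is 60-80 bpm. True maximal heart rate is 220 - age, then varied by 10 bpm either way.

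**Check of the stated design.** MICT lasts 1 + 36 + 4 = 41 min and HIIT 5 + 4×8 + 4 = 41 min, as stated. The HIIT cycles average (70 + 30)/2 = 50% MEC, which matches the MICT load. The sessions are therefore coherent relative to MEC, and the question is only what MEC represents.

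**Stop heart rate.**
- Age 30: 0.85 × 190 = 161.5 bpm, which is 28.5 below predicted maximum.
- Age 35: 0.85 × 185 = 157.25 bpm, which is 27.75 below.

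**Fraction of true maximal work at the stop,** f = (stop - rest)/(max - rest):

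| Age | Rest | f | 70f | 50f | 30f |
|---|---|---|---|---|---|
| 30 | 60 | 101.5/130 = 0.781 | 54.7 | 39.0 | 23.4 |
| 30 | 80 | 81.5/110 = 0.741 | 51.9 | 37.0 | 22.2 |
| 35 | 60 | 97.25/125 = 0.778 | 54.5 | 38.9 | 23.3 |
| 35 | 80 | 77.25/105 = 0.736 | 51.5 | 36.8 | 22.1 |

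**Gap between HIIT bout and MICT.** The nominal gap is 70 - 50 = 20 points. It becomes 20f = 14.7-15.6 points, a shrinkage of 1 - f = 22-26%.

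**Sensitivity.** With true maximum 10 bpm above or below 220 - age, f runs from 77.25/115 = 0.672 to 101.5/120 = 0.846. The bouts are then 47-59% of true maximum, MICT 34-42%, and the gap 15-33% smaller.

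**Between participants.** For the same named percentage, a man tested to exhaustion works at 1/f = 1.28-1.36 times the relative load of one stopped at 85% (base case).

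**Within a participant.** One MEC scales both of a man's sessions, so f cancels from the ratio 70:50:30. The crossover comparison stays like with like.

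**Ramp duration.** If true maximal work rate equals predicted, time to the 85% stop is divisor × f: 5.9-6.2 min for divisor 8, 7.4-7.8 for 10, 8.1-8.6 for 11 and 8.8-9.4 for 12. The 85% stop misses the 8-min lower limit for divisors 8 to 10 but fits the window for 11 and 12.

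**Heart rates that would separate the two cases (base case).** Stopped at 85%, rest + 0.7 × (stop - rest) gives 128-137 bpm in the bouts, and the same formula with 0.5 gives 109-121 bpm in MICT. Tested to exhaustion, with max in place of stop, the bouts are 148-157 and MICT 123-135 bpm.

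**The case against.** The strongest reply is that a near-maximal test is probably intended. Participants are encouraged to continue, three items are lower bounds on heart rate, RER and RPE that can be read as minimum effort, the ramp is scaled to predicted maximal work rate, and section 6.3 describes an effort-limited end. Much of this stands: intent is uncertain, and nothing shows how often the 85% item would end a test. It does not remove the point. The same list holds angina, serious arrhythmia and poor perfusion, which can only be reasons to stop, and any one item suffices.

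It is also fair that MEC is never tied to this test. A predicted or extrapolated maximum is not ruled out, so the link is an inference, though no other capacity test is scheduled.

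A reader might infer that the 85% stop is incompatible with the 8-12 min target. The documents do not support that. The divisor is chosen per person, and 11 or 12 fits.

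A conservative stop could be defended, since the test also serves as screening in sedentary men. But the safety stops already cover that purpose, under continuous ECG and clinician supervision. Finally, heart rate and gas exchange are already recorded in both sessions, so delivered intensity can be checked, although section 5 does not say that they will be used in this way.

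**Conclusion.** The point holds in conditional form. As written, section 5 lets the only capacity test end about 28 bpm below predicted maximal heart rate, in conflict with section 6.3, while both regimens are dosed against a maximum. If MEC is the peak of that test and the 85% criterion ends it, the 70/50/30% loads are about 52-55/37-39/22-23% of true maximum and the gap between HIIT bouts and MICT is 22-26% smaller (15-33% if true maximum is 10 bpm off prediction). These sizes are illustrations resting on a linear heart rate response and on resting and maximal rates that the protocol does not give.

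A reader might conclude that the HIIT-MICT comparison is biased, or that participants were in fact under-dosed. Neither follows. Each man's sessions share one MEC, and the protocol does not show which criterion ends the tests. What is exposed is the size of the delivered contrast, the accuracy of the intensity label and comparability between men. The wording should be corrected. It does not invalidate the design.

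**What to change.** - **Section 5, Cardiopulmonary exercise testing:** remove 85% of predicted maximal heart rate as a stop, and treat RER of at least 1.10 and RPE of at least 17 the same way, since either can also end the test early. Keep all three as recorded evidence of adequate effort. Retain the safety stops, the plateaus, severe fatigue or dyspnoea, and the participant's request. State that the test is symptom-limited, in line with section 6.3.
- **Section 4.5:** add one sentence defining MEC as the peak work rate reached on that test.
- **Records:** for each participant, note the reason for stopping and the peak heart rate.
- **Dose check:** use the heart rate and gas exchange already collected at T3B and T5B to report delivered intensity in the 70% bouts and in MICT.

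The cost is a somewhat harder test for sedentary men, already supervised with continuous ECG. No visit, sample or participant is added. For men already tested, the test cannot be changed, but the T3B/T5B intensity check remains possible.
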